**Abbreviations used in the protocol**

APACHE II Score: Acute Physiology And Chronic Health Evaluation II Score

BGA: Blood gas analysis

C: concentration

CE: administrative marking for medical products approved in the European Union

Cl: Clearance

Cltotal: total clearance between the first hour and the end of 48 hours

Clmean: mean plasma clearance

CRP: C-reactive protein

CVVH: continuous veno-venous hemofiltration

CVVHD: continuous veno-venous hemodialysis

CRRT: continuous renal replacement therapy

EMiC: Enhanced Middle Molecule Clearance

Hb: Hemoglobin

Hct: Hematocrit

IHD: intermittent hemodialysis

IL-6: Interleukin-6

KDIGO: Kidney Disease: Improving Global Outcomes

PCT: Procalcitonin

QB: Blood flow

QP: Plasma flow

RRT: renal replacement therapy

SAPS II-Score: Simplified Acute Physiology Score

SOFA-Score: Sequential Organ Failure Assessment Score

SPSS: Superior Performing Software System

**1. Introduction**

In critically ill patients, acute renal failure with a need for renal replacement therapy (RRT) is associated with a mortality rate of more than 50% (1). Acute renal failure is an independent risk factor for death in this patient population (2). Continuous renal replacement therapy (CRRT) is considered to have the theoretical advantage of better hemodynamic tolerance and effective fluid removal (3). However, it is not associated with a survival benefit compared to intermittent hemodialysis (IHD) (4). The current evidence does not allow any clear recommendation regarding the optimal dose (5, 6, 7, 8) and the best time point for starting RRT (3).

During CRRT, systemic anticoagulation to maintain the extracorporeal circuit, particularly in patients with an increased bleeding risk, can be a considerable challenge. In the last decade, regional citrate anticoagulation has been introduced as a practical and safe means for selective anticoagulation of the extracorporeal circuit (9). Citrate hemodialysis is associated with less bleeding (10), longer filter life span (11) and possibly improved survival (12). Therefore, citrate hemodialysis is generally recommended in the current KDIGO guidelines if systemic anticoagulation is not required for other reasons and there is no contraindication against citrate application.

Citrate is metabolized to bicarbonate in the intermediate metabolism. However, the physiologic citrate metabolism may be impaired in patients with reduced liver function, such as in septic shock or decompensated cirrhosis of the liver. Significantly lower blood flow, therefore less citrate, is required in hemodialysis than in hemofiltration. Therefore, regional citrate anticoagulation has been limited to continuous veno-venous hemodialysis (CVVHD) in order to reduce the citrate load to the critically ill. However, compared to continuous veno-venous hemofiltration (CVVH), middle molecule clearance is inadequate with CVVHD (13), which may be unfavorable in septic patients. A special high-cutoff dialyzer (EMiC®2) has thus been developed to overcome this issue.

The aim of this prospective randomized single-center trial is to investigate the middle molecule clearance rates with CVVHD using high-cutoff EMiC®2 dialyzer versus those of CVVHD using the classic high-flux dialyzer, both with regional citrate anticoagulation. The concept of citrate-based CVVHD with the EMiC®2 dialyzer may be an option to combine the advantages of the classic citrate CVVHD and CVVH. The trial is investigator-initiated and it will be conducted according to the German medical device law.

**2. Endpoints**

**Primary endpoint**: Does a citrate-based CVVHD with the EMiC®2 high-cutoff dialyzer lead to a better middle molecule clearance than a citrate-based CVVHD with a high-flux dialyzer, with β2-microglobulin as a marker molecule?

**Secondary endpoint:** Clearance rates of other molecules with different molar masses (urea, creatinine, myoglobin, IL-6 and albumin) using the EMiC®2 high-cutoff dialyzer compared to that of CVVHD with high-flux dialyzer.

**3. Patients and Methods**

Critically ill patients fulfilling the criteria for RRT will be consecutively screened (see inclusion criteria below). Using a 1:1 envelope randomization, patients will be assigned to either classic high-flux citrate-based CVVHD (group 1) or to citrate-based CVVHD using the high-cutoff EMiC®2 dialyzer (group 2). Patients who are screened but excluded from the trial will be recorded in a log book.

After inserting a hemodialysis catheter, CVVHD (multi**Filtrate®, Fresenius, Germany)** will be started using either the **polysulfone** Ultraflux® AV 1000S **high-flux dialyzer in group 1 or the polysulfone** Ultraflux EMiC®2 high-cutoff dialyzer in group 2 (both from Fresenius Medical care, Germany)**. A bicarbonate-buffered dialysate (Ci-Ca® Dialysate K4, Fresenius Medical Care, Germany**) will be used.

Regional anticoagulation in the extracorporeal circuit will be achieved through modification of the post-filter ionized calcium (Ca2+) concentration by adding a citrate solution (target post-filter Ca2+: 0.25 – 0.3 mmol/l).

The dialysate flow will be 25 ml/kg body weight (14). The blood flow (QB) will be adjusted at threefold of the dialysate flow. A calculator program will be available for the study group. The extent of the ultrafiltration will be adjusted based on the condition of the patient and the decision of the treating physician. The dialysis system will be changed every 72 hours at the latest according to the instructions of the manufacturer.

Simultaneous measurements of urea, creatinine, β2-microglobulin, myoglobin, interleukin-6 and albumin will be conducted 1 (t0), 6 (t1), 12 (t2), 24 (t3) and 48 hours (t4) after the start of CVVHD from samples drawn immediately before (pre-filter) and after the dialyzer (post-filter). The samples will be provided with a study-specific code and immediately sent to the laboratory.

The plasma flow (Qp) will be calculated using the following formula based on the individual hematocrit:

Qp= QB x (1-Hct/100)

The substance-specific clearance (Cl) due to RRT at the above mentioned time points will then be calculated using the following formula:

Cl (ml/min) = QP x ([Cprefilter- Cpostfilter]/ Cprefilter)

The total clearance (Cltotal) from t0 to t4 will then be computed using the following formula:

Cltotal = (((Cl1h + Cl6h) / 2) * 5 * 60) + (((Cl6h+ Cl12h) / 2) * 6 * 60) + (((Cl12h+ Cl24h) / 2) *

12 * 60) + (((Cl24h + Cl48h) / 2) * 24 * 60)

The mean plasma clearance (Clmean) in ml/min will then be derived from the above data as follows:

Clmean = Cltotal /47/60

Furthermore, data for filter life span, duration of RRT, interruptions of RRT as well as the course of markers of systemic inflammation will be collected.

Based on statistical calculations from pilot data, a sample size of 60 with 30 patients in each arm is planned.

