**4. Data compilation**

Patient data will be documented anonymized in a data base. Additional to the clearance variables mentioned earlier, the following data will be documented for every patient:

- Age, gender, height, weight
- Major diagnosis
- Indication for RRT
- ICU scores
  - on study inclusion: APACHE II score, SAPS II score, SOFA score
  - daily: SOFA score, SAPS II score until ICU discharge
- pre-existent end-stage renal disease (predefined subgroup analysis)
- location of the vascular access
- daily laboratory assessment (at 5 am):
  - hemoglobin, hematocrit, white cell count, platelet count
  - blood urea, creatinine
  - Na+, K+, Cl-, PO43-, Ca2+, Mg2+
  - BGA every 6 hours
  - Serum CRP, PCT, IL-6, albumin
- Hemodialysis protocol with 6-hourly documentation of blood flow (ml/min), dialysate flow (ml/h), ultrafiltration (ml/h), citrate infusion rate, calcium substitution rate, transmembrane pressure, pre- and post-filter Ca2+.
- Filter life span
- Duration of RRT interruptions
- ICU and hospital length of stay
- ICU, hospital, 28- and 90-day survival
- Status of renal function (>96 hours RRT-free period)

The statistical analysis will be carried out using the program package SPSS for Windows.

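### The clearance formula holds only without net ultrafiltration, which the protocol permits, so a term is missing from the primary and all secondary clearances

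*Protocol*

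**What the plan says.** Section 3 (Patients and Methods) derives plasma flow from blood flow and hematocrit, "Qp= QB x (1-Hct/100", and then clearance at 1, 6, 12, 24 and 48 hours as "Cl (ml/min) = QP x ([Cprefilter- Cpostfilter]/ Cprefilter". These values feed Cltotal and Clmean. They apply to β2-microglobulin, the marker for the primary endpoint, and to urea, creatinine, myoglobin, IL-6 and albumin (section 2, Endpoints).

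On fluid removal, the same section states: "The extent of the ultrafiltration will be adjusted based on the condition of the patient and the decision of the treating physician". It gives no rate or range. The concentrations come from "samples drawn immediately before (pre-filter) and after the dialyzer (post-filter". Anticoagulation is achieved "by adding a citrate solution (target post-filter Ca2+: 0.25 – 0.3 mmol/l", but the position of the citrate port relative to the pre-filter sample is not given.

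Section 4 (Data compilation) plans "Hemodialysis protocol with 6-hourly documentation of blood flow (ml/min), dialysate flow (ml/h), ultrafiltration (ml/h"; the same item also lists the citrate infusion rate. No ultrafiltration correction to the clearance formula appears anywhere in the protocol.

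**The concern.** The formula multiplies the fractional fall in concentration by inlet plasma flow. When water is removed across the membrane, less plasma leaves than entered, and the solute left behind is concentrated in it. Part of what was cleared is then hidden by a higher post-filter concentration.

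Ultrafiltration above zero should be common in this trial. The inclusion criteria name life-threatening water disorders as a reason to start treatment, and the introduction lists fluid removal among the advantages of the continuous technique.

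At stake are the absolute clearances the trial will report and, to a lesser degree, the contrast between filters. The protocol itself fixes the formula, so this is not a detail it leaves to an analysis plan.

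**Working it through.** **Plan's own figure.** The intervals in Cltotal are 5 + 6 + 12 + 24 = 47 h, which matches the divisor in Clmean. Clmean is therefore a weighted mean of the five clearances, with weights 2.5, 5.5, 9, 18 and 12 over 47 (sum 1). A bias of constant size at each draw passes into Clmean unchanged.

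**Mass balance.** Let K be true clearance, QUF the fluid removed across the filter, and ignore citrate volume for now.

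- QP × Cpre = (QP − QUF) × Cpost + K × Cpre
- Hence K = QP × (Cpre − Cpost)/Cpre + QUF × Cpost/Cpre. The second term is absent from the protocol.
- Since Cpost/Cpre = (QP − K)/(QP − QUF), the protocol's formula returns QP × (K − QUF)/(QP − QUF).

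**Inputs.**

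- From section 3: "The dialysate flow will be 25 ml/kg body weight (14" and "The blood flow (QB) will be adjusted at threefold of the dialysate flow". No time unit is printed for the dialysate flow; it is read here as per hour.
- Assumed: 80 kg, hematocrit 30%, QUF 50–300 ml/h, and true clearances of 10 and 20 ml/min for the two filters.
- Dialysate flow = 25 × 80/60 = 33.3 ml/min; QB = 100 ml/min; QP = 100 × 0.70 = 70 ml/min.

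**Worked case at QUF 100 ml/h (1.67 ml/min).**

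- True 20: 70 × (20 − 1.67)/(70 − 1.67) = 18.8 (−6%). The missing term is 1.67 × 50/68.33 = 1.22.
- True 10: 70 × (10 − 1.67)/68.33 = 8.5 (−15%). The missing term is 1.46.
- True 0: 70 × (−1.67)/68.33 = −1.7.

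| QUF (ml/h) | True 20 reads | True 10 reads | Difference (true 10) | True 0 reads |
|---|---|---|---|---|
| 50 | 19.40 | 9.28 | 10.12 | −0.84 |
| 100 | 18.78 | 8.54 | 10.24 | −1.71 |
| 200 | 17.50 | 7.00 | 10.50 | −3.50 |
| 300 | 16.15 | 5.38 | 10.77 | −5.38 |

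**Equal ultrafiltration in both arms.** At the same QP and QUF, the difference is multiplied by QP/(QP − QUF): +1.2%, +2.4%, +5.0% and +7.7% in the four rows. At 60 kg, hematocrit 40% and 300 ml/h, QP = 75 × 0.60 = 45 and QUF = 5, giving 45/40 = 1.125 (+12.5%). The factor is positive, so the sign cannot reverse.

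**Unequal ultrafiltration.** If both filters truly clear 15 ml/min and mean QUF is 0 in one arm and 100 ml/h in the other, the readings are 15.00 and 13.66, a spurious difference of 1.34 ml/min. At true clearances of 20 and 10 the shift is 1.22 and 1.46.

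**Citrate.** Assume a citrate inflow Qc of 3 ml/min, QUF 100 ml/h, and true clearance 15 ml/min relative to the sampled pre-filter concentration.

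- Sample downstream of the port: Cpost/Cpre = (73 − 15)/(73 − 1.67) = 0.813, so the formula gives 70 × 0.187 = 13.08. The understatement grows.
- Sample upstream: Cpost/Cpre = (70 − 15)/(73 − 1.67) = 0.771, so the formula gives 16.03. The bias reverses, and a zero-clearance molecule reads +1.31.

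**The case against.** The strongest reply is that the primary question is directional and the contrast is barely touched. With similar ultrafiltration in both arms the difference grows by a few percent. If the filters clear equally, the expected difference stays zero, so no false superiority arises. That stands. It does not rescue the absolute clearances in ml/min, which are what Cl and Clmean are defined to measure.

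An imbalance as large as 100 ml/h is also unlikely by chance. With an assumed between-patient SD of 60–100 ml/h and 30 per arm, the standard error of the difference is SD × √(2/30), about 15–26 ml/h. An imbalance of one standard error shifts the contrast by roughly 0.2–0.35 ml/min (1.34 × 0.155 to 1.34 × 0.258). A larger shift needs prescribing that differs systematically by arm. No blinding is described, but the protocol gives no reason to expect this.

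Several stronger readings are tempting, and the document does not support them:

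- That every clearance is understated. This needs net ultrafiltration above zero and a pre-filter sample downstream of the citrate port. Sampling immediately before the dialyzer suggests that position but does not settle it.
- That the high-flux arm always loses most. This needs lower clearance in that arm and similar QP and QUF in both arms.
- That albumin clearance will be negative. This needs true albumin clearance below QUF, which is plausible for a largely retained molecule, but the protocol gives no figure.
- That a true ratio of 2.0 would be reported as 2.5 (17.5/7.0 at 200 ml/h). The arithmetic is right, but no ratio analysis is stated and the inputs are assumed.

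Finally, ultrafiltration is already recorded 6-hourly, so much of the correction can be recovered. That makes the fix cheap; it does not make the formula right.

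**Conclusion.** The formula is wrong as written for any patient with net ultrafiltration, and it defines the primary variable and all five secondary clearances. With the sample downstream of the citrate port, each clearance is understated by QUF × Cpost/Cpre, or somewhat more once citrate volume is counted. Under the stated assumptions at 100 ml/h, the loss is about 1.2 ml/min on a true 20 and 1.5 ml/min on a true 10. Molecules cleared more slowly than QUF read negative.

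The effect on the EMiC®2 minus high-flux difference is modest when ultrafiltration is equal: about 1–5% at 50–200 ml/h for QP 70, up to 12.5% at the extreme examined, with no change of sign. That protection is lost to the extent that ultrafiltration differs between arms.

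The missing term follows from the protocol alone. Its size rests on assumed weight, hematocrit, ultrafiltration rate and clearances, and its direction on the unstated sampling position.

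**What to change.** Compute, at each time point and for all six molecules, Cl = QP × (Cpre − Cpost)/Cpre + QUF × Cpost/Cpre, and derive Cltotal and Clmean from the corrected values. Specify that:

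- QUF is in ml/min and is the total fluid removed across the filter. State whether the recorded ultrafiltration is this quantity or net removal from the patient.
- QP is the plasma-side inflow at the pre-filter sampling point, including citrate inflow if the sample is downstream of the citrate port. If it is upstream, citrate enters between the two samples, and the second term becomes (QUF − Qc) × Cpost/Cpre.
- The position of the pre-filter sampling port relative to the citrate port is stated.
- QB, QUF and citrate rate are recorded at each draw. The 6-hourly record can coincide with the 6, 12, 24 and 48 h samples, but the 1 h sample may fall outside it.

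The cost is one formula term, a sentence on the sampling port, and a few extra entries per draw; treatment does not change. The downside is comparability. If the pilot values behind the sample size of 60 used the uncorrected formula, they are not directly comparable and should be recomputed where ultrafiltration was recorded.

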**Inclusion criteria**

The inclusion criteria are based on the current KDIGO guidelines for initiation of extracorporeal renal support. RRT should be started as soon as possible in patients with life-threatening water, electrolyte and/or acid-base disorders (14)

**Exclusion criteria**

- Therapeutic anticoagulation required for reasons other than RRT
- Age <18 years
- Expected high risk for citrate accumulation (e.g. severe acute liver failure)
- RRT considered contraindicated (e.g. terminal malignant disease) or rejected by the patient
- Morbid patient with a high likelihood to die within 48 hours
- Pregnancy and lactation
- Participation in another trial
- Refusal to participate in the study

RRT will not be delayed for the sake of this trial. If a patient cannot be included in the trial at the beginning of the first RRT course, a study inclusion is still possible at a later time, for example after the regular filter change, if the indication for RRT persists.

**Inclusion algorithm**

Indication for CRRT

Patient can give consent

Patient is not able to give consent

Informed consent given

No consent

Study inclusion

No study inclusion

Legal guardian is available

No legal guardian

Urgent institution of a legal guardian

**Risk-benefit assessment**

Improved clearance of larger molecules with CVVHD using the high-cutoff dialyzer EMiC®2, combining the benefits of regional citrate anticoagulation and CVVH, may possibly have an advantage in certain disease states, such as sepsis or rhabdomyolysis. Based on current knowledge, specific risks due to this intervention are not expected. The EMiC®2 dialyzer is approved for citrate-based hemodialysis and it has already received the official CE marking.

A maximum of 50 ml blood sample is required within the maximum study CRRT period of 48 hours. These blood samples will be drawn from the extracorporeal circuit, thus pain-free to the patient. Further study procedures are not planned.

**4. Data compilation**

Patient data will be documented anonymized in a data base. Additional to the clearance variables mentioned earlier, the following data will be documented for every patient:

- Age, gender, height, weight
- Major diagnosis
- Indication for RRT
- ICU scores
  - on study inclusion: APACHE II score, SAPS II score, SOFA score
  - daily: SOFA score, SAPS II score until ICU discharge
- pre-existent end-stage renal disease (predefined subgroup analysis)
- location of the vascular access
- daily laboratory assessment (at 5 am):
  - hemoglobin, hematocrit, white cell count, platelet count
  - blood urea, creatinine
  - Na+, K+, Cl-, PO43-, Ca2+, Mg2+
  - BGA every 6 hours
  - Serum CRP, PCT, IL-6, albumin
- Hemodialysis protocol with 6-hourly documentation of blood flow (ml/min), dialysate flow (ml/h), ultrafiltration (ml/h), citrate infusion rate, calcium substitution rate, transmembrane pressure, pre- and post-filter Ca2+.
- Filter life span
- Duration of RRT interruptions
- ICU and hospital length of stay
- ICU, hospital, 28- and 90-day survival
- Status of renal function (>96 hours RRT-free period)

The statistical analysis will be carried out using the program package SPSS for Windows.

**Funding**

This trial is funded by an unrestricted grant from Fresenius Medical Care Deutschland GmbH, [name], Germany. The sponsor does not have any influence on any part of the trial.

